## ABSTRACT

**OBJECTIVE:** to compare endocervical brushing with endocervical curettage with respect to diagnostic and patient discomfort.

**METHOD:** women referred to colposcopy because of abnormal Papanicolaou tests will be randomized to endocervical sampling with either a metal curette (endocervical curettage -ECC) or an endocervical brush. All samples will be submitted for histological study.

**EXPECTED RESULTS:** higher specimen adequacy and lower patient discomfort with the endocervical brush.

# **RANDOMIZED COMPARISON OF ENDOCERVICAL EVALUATION WITH THE CURETAGE AND BRUSH FOR THE DIAGNOSIS OF DYSPLASIA OF THE UTERINE CERVIX**

## **INTRODUCTION**

In the last decade significant advances in the diagnosis of cervical cancer and pre-invasive disease have been made. One of the fundamental steps in diagnosis is colposcopy with the evaluation of the endocervical canal. This is usually done by endocervical curettage (ECC), but due to its high rate of false positive and false negative results and important patient discomfort, efforts have been made to find alternative techniques.

## **OBJECTIVE**

The objective of this study is to compare the adequacy of specimen of the endocervical brush versus the endocervical curette in the evaluation of the endocervical canal during routine colposcopy done in patients with suspicion of dysplasia. The second end point of this study is to evaluate patient and doctor discomfort with these two methods.

## **ACTUAL KNOWLEDGE IN THE DOMAIN**

In the last decade, no more than 10 original articles have been written comparing endocervical curette with endocervical brush. The design of these studies has been very variable in terms of recollection techniques and analysis of specimen.

### **Recollection technique**

Boardman[1], and Tate[2] used a sequential method for recollection of material, either by using first the curette and then recollecting the material with a brush or the opposite, while Mogensen [3] and Klam [4] used either one or the other. They all found that endocervical sampling with a cytobrush had similar sensitivity and specificity to traditional endocervical curettage. The sensitivity and specificity with

the brush was even higher when using a sleeved cytobrush.

### Analysis of specimen

Boardman [1] did a different analysis for the brush and the curette (cytology for the first and histology for the second) while Klam [4], Gibson [5], Maksem [6] and Mogensen [3] all did histological analysis of both samples. This is very important, because it has been demonstrated that when analyzed as cytology, cytobrush technique tends to have high false positive rate. Of all these groups, only Maksem [6] recollected their brush specimen into a liquid fixative process; all others fixed the material onto a slide.

Klam [4] et al evaluated the discomfort associated with each technique, and came to the conclusion that there was no difference.

### STUDY DESIGN

This is a prospective randomized study, whose target population is all women consulting our colposcopy clinic. The eligibility of each patient will be analyzed based of the following characteristics:

#### Inclusion criteria

- French-speaking
- 21 years or older
- Attending our colposcopy clinic
- Need for endocervical evaluation
- Full autonomy or capacity to understand the procedures

#### Exclusion criteria

- Pregnancy
- Absence of uterus
- History of DES exposure in utero

Information will be given to the patients before commencing their colposcopy, and informed consent will be obtained. Once the colposcopist has decided that a further

evaluation of the endocervical canal is needed, women will then be randomized to either the ECC or the ECB groups. ECC will be performed maximum 3 times with a Novak metal curette using short, firm strokes from the lower uterine segment down to the external os, circumferentially. Samples will then be collected in CARNOY. Endocervical brushing will be performed by taking 12 swipes of the entire length of the endocervical canal while rotating simultaneously the brush. The specimen will then be collected and fixed with Thin Prep. Cytological and histological interpretation of the ECB specimens will then be performed, while for the ECC specimens only histological interpretation will be done. The adequacy of the specimens will be based on the quantity of endocervical cells present ( $<$  or  $\geq$  20 endocervical cells), the quantity of histological material ( $<$  or  $\geq$  3 epithelial stripes) and the quality of histological material (absence or presence of lamina propia).

To evaluate the degree of patient discomfort patients will be requested to complete a questionnaire once the exam has been completed. The main acceptance variables will be degree of helplessness, pain (on visual analog scales), willingness to undergo the test again, and overall satisfaction. Once the exam has been completed, the doctor performing the sampling will answer a questionnaire indicating his/her perception of the exam (patient's pain, technical difficulty performing the exam, doctors acceptability of the exam).

### Statistical analysis

The statistical analysis will be based on the comparison of the performance of both tests. The main outcome variable will be the proportion of a satisfactory sample in each group. A satisfactory specimen will be defined by the pathologist as indicated in the paragraph "study design". To demonstrate a 20% difference (with 80% power and a risk of type 1 error set at 5%) in the quality of the material obtained with the brush, we will need a total of 180 patients.

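### The pathologist calls the primary outcome after a work-up that probably reveals the device, and no masking step is described, so borderline adequacy calls can be biased in either direction

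*Protocol*

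**What the plan says.** The Statistical analysis section of the Protocol names the endpoint: "The main outcome variable will be the proportion of a satisfactory sample in each group". It then says who decides: "A satisfactory specimen will be defined by the pathologist as indicated in the paragraph" on study design.

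The criteria stand in the procedures text under Exclusion criteria, within Study design. "The adequacy of the specimens will be based on the quantity of endocervical cells present", with a cut-off of 20. Two histological items follow: fewer than 3, or at least 3, epithelial strips; and "the quality of histological material (absence or presence of lamina propia").

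The same text sets a different laboratory route for each arm. For the curette: "Samples will then be collected in CARNOY". For the brush: "The specimen will then be collected and fixed with Thin Prep". The readings also differ: "Cytological and histological interpretation of the ECB specimens will then be performed, while for the ECC specimens only histological interpretation will be done".

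The Abstract gives the investigators' expected result as "higher specimen adequacy and lower patient discomfort with the endocervical brush", and the Expected contribution section repeats the hope that the brush is superior. The Protocol describes no coding of specimens, masking of the pathologist, second reading or agreement check.

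**The concern.** The primary outcome is a reading made by a person, and the route each specimen takes through the laboratory differs by arm in two visible ways: the fixative, and the presence or absence of a cytology preparation. A pathologist who follows the plan as written will probably know the device when deciding whether the specimen is satisfactory.

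Most specimens will be clearly above or below the cut-offs. Near them (two or three strips in fragmented material, about 20 cells, a doubtful piece of stroma) the call needs judgement, and what the pathologist expects of the device can enter it. A shift of this kind goes straight into the estimated difference between arms. A larger sample does not remove it, and no later analysis can restore masking. How slides are labelled and in what order they are read is trial conduct, so it belongs in the Protocol and cannot be left to an analysis plan.

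**Working it through.** **1. Does the plan reveal the arm?**

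| Step | Curette | Brush |
|---|---|---|
| Collected or fixed in | Carnoy | Thin Prep |
| Readings | Histology | Cytology and histology |
| Coding or masking before the adequacy call | None described | None described |

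Either of the first two rows is enough to identify the arm if the pathologist sees it. The document does not say what the pathologist sees, so knowledge of the arm is a strong inference and not a stated fact.

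**2. The plan's own figure.** The Protocol gives 180 patients for a 20% difference, 80% power and 5% type I error. It states no control rate, allocation ratio or sidedness. I read 20% as 20 percentage points and assume 1:1 allocation. The two-sided pooled-variance formula without continuity correction then gives a total of 178 for 25% against 45%, and 178 for 55% against 75%. Over lower rates of 5% to 75% the total runs from 98 to 194. So 180 is plausible for some control rates but cannot be confirmed. The present point does not depend on it, and masking would not change it.

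**3. Size of a possible bias (illustration).** Let *s* be the share of specimens that are borderline, and *g* the gap between arms in the proportion of borderline specimens passed when true adequacy is equal. Then

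bias = *s* × *g*.

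Neither input is in the document; both are assumed.

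| *s* | *g* | Bias | As a share of the 20-point target |
|---|---|---|---|
| 0.10 | 0.10 | 0.01 | 1/20 = 5% |
| 0.20 | 0.10 | 0.02 | 2/20 = 10% |
| 0.10 | 0.50 | 0.05 | 5/20 = 25% |
| 0.20 | 0.50 | 0.10 | 10/20 = 50% |

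The sign is open. The same sizes apply if the pathologist marks brush material down.

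**4. Effect on the test (illustration).** Assume 90 per arm, no true difference, a two-sided 5% test, true adequacy *p* in both arms, and a reading shift *b* in favour of the brush. The chance of a significant result for the brush is

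Φ[(*b* − 1.96 × SE0) / SE1],

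where SE0 = √[*m*(1 − *m*) × 2/90] with *m* = *p* + *b*/2, and SE1 = √{[*p*(1 − *p*) + (*p* + *b*)(1 − *p* − *b*)]/90}.

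For *p* = 0.60 and *b* = 0.10: SE0 = √(0.65 × 0.35 × 2/90) = 0.0711; SE1 = √[(0.24 + 0.21)/90] = 0.0707; (0.10 − 1.96 × 0.0711)/0.0707 = −0.557; Φ = 0.289.

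| Shift *b* | Chance of a false brush win, *p* from 0.40 to 0.80 |
|---|---|
| 0 | 2.5% |
| 1 point | 3.4% to 3.7% |
| 2 points | 4.5% to 5.3% |
| 5 points | 10% to 14% |
| 10 points | 27% to 47% |

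To see what such a shift asks of the pathologist: at *p* = 0.70, 5 points means 0.05/0.30 = 0.167, or about 1 in 6 truly unsatisfactory brush specimens called satisfactory. A shift against the brush would act the other way and hide part of a true advantage.

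**The case against.** The strongest reply is that the criteria are fixed in advance and are not a global impression: two counts with cut-offs, and one item scored as absent or present. That stands, and it confines the problem mostly to borderline specimens, whose frequency the document does not give. It does not remove the problem, because counts in fragmented material need judgement near a cut-off. The text also says only that adequacy is based on the three items, without a rule for combining them, so a specimen that passes some and fails others is also left to the pathologist.

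Three stronger readings are tempting and should be resisted.

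- A reader might infer that the pathologist knows the arm for every specimen. The Protocol does not say how slides are labelled, or whether one person reads both cytology and histology. What is supported is that the work-up probably reveals the arm and that nothing described prevents it.
- A reader might infer that the bias must favour the brush. The Abstract and Expected contribution record what the investigators expect; no section records what the pathologist expects. The Introduction calls curettage the usual method, and the Ethical issues section rates the risk of inadequate sampling as equal for slide-technique cytology. A pathologist used to curettings could mark brush material down.
- A reader might take 10 points, half the target difference, as the expected bias. It is the top of an assumed range, and smaller assumptions give 1 point.

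It can also be said that the brush arm's extra cytology and the missing combining rule are a larger asymmetry. They are a separate matter, which masking would not cure, but they do not make an unmasked reading harmless.

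**Conclusion.** The point holds in a limited form. The primary outcome depends partly on the pathologist's judgement, the planned work-up probably discloses the device, and no coding or masking is described. Knowledge of the device can therefore bias borderline adequacy calls in either direction. The size is unknown. With 10% to 20% borderline specimens and a 10- to 50-point gap in pass rates, both assumed, it is 1 to 10 points against a target of 20. If the shift favours the brush and there is no true difference, the chance of a false brush win rises from 2.5% to between about 3% and 47%, given 90 per arm and true adequacy of 40% to 80%. This does not show that the trial will be biased. It shows a weakness in the primary endpoint that is cheap to reduce and should be dealt with before specimens are read.

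**What to change.** Add a short reading procedure to the Protocol.

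1. The laboratory labels the histology slides of both arms with a study code only, with no device, fixative or request-form details.
2. The pathologist records the strip count and lamina propria on an adequacy form from the coded slide, before seeing the cytology, the fixative or the request form. The same pathologist then issues the routine report.
3. The Protocol states on which preparation the 20 endocervical cells are counted. Only the strips and the lamina propria are described as histological, so treating all three as histological without saying so could redefine the endpoint in the brush arm. The coded histology slide in both arms is preferable. If the count is made on cytology in the brush arm, record it separately, after the masked histology items.

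Cost: relabelling the slides of about 180 patients and one short form. No extra pathologist is needed, and the sample size and routine reporting stay as they are. The downside is that masking will be partial, because tissue appearance may hint at the device.

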### ETHICAL ISSUES

The follow up of patients will not differ from guidelines already in use. The risk of inadequate sampling requiring a second exam has been evaluated as equal for both techniques when analyzing the cytology with the slide technique analysis.

### FINANCIAL CONSIDERATION

The cost of the different techniques used in this study is 93 francs for the analysis of the material obtained with the brush and 101 to 130 francs for the analysis of the material obtained with the curette, depending on the diagnosis. Both of these exams will be performed only if indicated during her colposcopic exam, and only one of these techniques will be used. The cost of these exams is covered by normal health insurance, and the actual cost for the patients will depend on their "franchise". The study will include no extra charge for the HUG.

### EXPECTED CONTRIBUTION

With this study we hope to demonstrate that endocervical sampling with cytobrush is superior to sampling with endocervical curette in term of diagnosis and patient comfort and doctors acceptability.

### COMMENTARY

The main investigators have signed up for the bio-statistic course organized in January 2012. Until that moment, the clinical side of the study will be closely supervised by Prof. [name], while the biostatistics will be supervised by Prof. [name]. Both professors have a vast experience in clinical trials, and [name], has also completed the course in GCP (Good Clinical Practice) in addition to a PhD in epidemiology.

